#### Inclusion criteria

Patient must have 1-3 asypmtomatic metastatic tumor(s) of the bone or soft tissue developed within the past 6-months that are ≤ 5.0 cm or < 250 cm^3.^
Patient must have had their primary tumor treated with surgery and/or radiation and salvage radiation to the prostate bed or pelvis is allowed.Histologic confirmation of malignancy (primary or metastatic tumor).Prostate specific antigen (PSA) ≥ 0.5 ng/mL but ≤ 50 ng/mL and Testosterone ≥ 125 ng/dL.PSA doubling time (PSADT) < 15 months. PSADT will be calculated using as many PSA values that are available from time of relapse (PSA > 0.2 ng/dL).Patient may have had prior systemic therapy and/or ADT associated with treatment of their primary prostate cancer. Patient may have had ADT associated with salvage radiation therapy.Patient must be ≥ 18 years of age, have the ability to understand, and the willingness to sign, a written informed consent document.Patient must have an Eastern Cooperative Oncology Group performance status ≤ 2.Patient must have normal organ and marrow function as defined as:Leukocytes >2,000/μL, absolute neutrophil count >1,000/μL, platelets >50,000/μL

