#### Exclusion criteria

No more than 3 years of ADT is allowed, with the most recent ADT treatment having occurred greater than 6 months prior to enrollment.
^18^F-DCFPyL-PET/MRI or ^18^F-DCFPyL-PET/CT scan within the past 6 months with results that demonstrate lesions not seen on baseline CT or bone scanCastration-resistant prostate cancer (CRPC).Spinal cord compression or impending spinal cord compression.Suspected pulmonary and/or liver metastases (greater > 10 mm in largest axis).Receipt of any other investigational agents or participation in a concurrent treatment protocol.Serum creatinine and total bilirubin > 3 times the upper limit of normalLiver Transaminases > 5-times the upper limit of normal.Inability to lie flat during or tolerate PET/CT, PET/MRI or SABR.Refusal to sign informed consent.

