### Evaluation of randomization and blinding

This study will employ a randomized phase II design to determine the appropriateness of a subsequent phase III trial based on comparison of rate of progression at 6 months. An interactive web response system (IWRS) will be utilized to obtain the patient’s randomization assignment. Randomization will occur in a 2:1 fashion for SABR and observation arms, respectively. A minimization approach [35] will be applied to ensure balanced assignment to each treatment arm by: 1) Initial treatment with surgery vs. radiation therapy; 2) Prior hormonal therapy vs. no prior hormonal therapy; and 3) PSADT <6 mos vs. 6-14.9 mos. The on-study date for protocol entry will be the day that the study subject is randomized. Patients will be re-evaluated for radiographic response 6 months after randomization. Trial radiologists evaluating for treatment responses will be blinded to the treatment group and treatment specifics. The trial radiologists and the principal investigator will be unblinded only if a patient progresses at any time during the study.

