#### Data analysis

##### 2.4.2.1.Analysis of primary objective

A minimization approach [35] will be applied to ensure balanced assignment to each treatment arm by: 1) Initial treatment with surgery vs. radiation therapy; 2) Prior hormonal therapy vs. no prior hormonal therapy; and 3) PSADT <6 mos vs. 6-14.9 mos. Baseline PSA level is defined as that measured Day 1 following randomization.The primary clinical outcome will be the proportion of patients who have progressed after 6 months from randomization. For each arm, we will calculate the proportion of patients who have progressed and extract 95% confidence intervals. If a patient has withdrawn from the study before 6 months, they will be considered to have progressed.Progression will be a composite endpoint defined from the Prostate Cancer Working Group 2 (PCWG2) criteria for mCRPC [38] and our previous trials in a population of men with biochemical failure without metastases [37–39]. Progression will be defined as either: 1) a ≥ 25% increase in PSA from nadir (and by ≥ 2 ng/mL), requiring confirmation ≥ 4 weeks later (PCWG2 criteria); and/or, 2) clinical/radiographic-progression defined as symptomatic progression (worsening disease-related symptoms or new cancer-related complications), or radiologic progression (on CT scan: ≥ 20% enlargement in sum diameter of soft-tissue target lesions [RECIST 1.1 criteria]; on bone scan: ≥ 1 new bone lesions), initiation of ADT or death due to any cause, whichever occurs first. Death is considered a severe adverse event here.We will compare the proportion of patients who have progressed in the observation and SABR arms using Fisher’s exact test. The analysis population includes all randomized subjects based on intention-to-treat.

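### The PSA doubling time rule has a relapse threshold in a conflicting unit (ng/dL) and does not say which relapse starts the window for men who had salvage radiation or ADT

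*Protocol article*

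**What the plan says.** The Inclusion criteria of the protocol article require "PSA doubling time (PSADT) < 15 months" and give the method: "PSADT will be calculated using as many PSA values that are available from time of relapse (PSA > 0.2 ng/dL". The same list sets the PSA range for entry as "Prostate specific antigen (PSA) ≥ 0.5 ng/mL but ≤ 50 ng/mL". The composite progression definition in section 2.4.2.1 also works in ng/mL: "a ≥ 25% increase in PSA from nadir (and by ≥ 2 ng/mL". So do the PSA limits under Response criteria.

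On earlier treatment, the Inclusion criteria state that "salvage radiation to the prostate bed or pelvis is allowed" and "Patient may have had ADT associated with salvage radiation therapy". The Exclusion criteria add: "No more than 3 years of ADT is allowed, with the most recent ADT treatment having occurred greater than 6 months prior to enrollment".

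PSADT is used twice. It is an entry criterion, and it is one of the three minimisation factors, split as "PSADT <6 mos vs. 6-14.9 mos" (Evaluation of randomization and blinding, repeated in section 2.4.2.1). Prior hormonal therapy is another of the three.

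**The concern.** A doubling time describes one exponential rise. A man who relapsed after primary treatment, had salvage radiation with or without ADT, and then relapsed again has two rises with a treated period between them. The rule asks for as many values as are available but leaves open which relapse starts the count. It does not exclude values taken before or during salvage treatment. Sites may therefore reach different PSADTs from the same PSA history.

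The unit adds a separate problem. If the threshold is applied as printed, nearly any detectable PSA counts as relapse, so low, suppressed values enter the fit.

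At stake are entry at the 15-month limit, the stratum at the 6-month cut, and a consistent meaning of PSADT in men with and without prior hormonal therapy.

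**Working it through.** **1. The article's own design figure.** With 36 versus 18 men, progression of 40% versus 80% and one-sided alpha 0.05, exact enumeration of Fisher's test gives 85.06% power, against the stated 85%. This figure does not use PSADT, so nothing below changes it.

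**2. Unit.** 1 dL = 100 mL, so 0.2 ng/dL = 0.2/100 = 0.002 ng/mL. This is 0.2/0.002 = 100 times below 0.2 ng/mL and 0.5/0.002 = 250 times below the entry minimum of 0.5 ng/mL.

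**3. Effect of the literal unit alone (assumed series).** PSADT = ln 2 / b, where b is the least-squares slope of ln(PSA) on months. Assume quarterly values, flat at 0.03 ng/mL for 24 months, then a steady rise, with the last value below 5 ng/mL.

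| True PSADT (months) | 3 | 4 | 5 | 6 | 8 |
|---|---|---|---|---|---|
| Values > 0.002 ng/mL | 6.6 | 7.4 | 7.8 | 8.7 | 10.3 |
| Values > 0.2 ng/mL | 3.0 | 4.0 | 5.0 | 6.0 | 8.0 |

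Men with a true 3, 4 or 5 months cross the 6-month cut. Men with 6 or 8 months keep their stratum and eligibility.

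**4. Effect of the window (assumed series).** Quarterly values. The first rise starts at 0.2 ng/mL with a 6-month doubling time. PSA is then held at 0.1 ng/mL under treatment. It next rises from 0.1 ng/mL with the true current PSADT, and the last quarterly value is at or below a ceiling.

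- A: first rise 3 months, suppression 12 months, ceiling 30 ng/mL.
- B: first rise 12 months, suppression 12 months, ceiling 10 ng/mL.
- C: first rise 12 months, suppression 24 months, ceiling 5 ng/mL.

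PSADT from all values since the earliest relapse:

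| True PSADT (months) | 3 | 4 | 5 | 6 | 8 | 10 |
|---|---|---|---|---|---|---|
| A | 5.0 | 6.1 | 6.8 | 7.6 | 9.5 | 11.3 |
| B | 12.5 | 12.5 | 11.5 | 12.3 | 14.1 | 15.4 |
| C | 30.6 | 22.8 | 20.2 | 19.2 | 19.1 | 21.0 |

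Worked cell (C, true 4 months): 5 values from 0.2 to 0.8 ng/mL (months 0-12), 8 values at 0.1 (months 15-36) and 7 values from 0.17 to 3.8 (months 39-57). The slope over all 20 values is 0.0304 per month, and 0.693/0.0304 = 22.8. The slope over the last 7 values is 0.1733, and 0.693/0.1733 = 4.0.

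- All 18 values are inflated. Those at or above 15 months number 0 of 6 in A, 1 of 6 in B and 6 of 6 in C.
- Of the men with a true PSADT below 6 months, two of three in A and all three in B land in the 6-14.9 month stratum.
- Using only post-treatment values above 0.2 ng/mL returns the true PSADT in all 18 series, from 4 to 24 values.

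**5. Does correcting the unit cure the window?** No. Keeping only values > 0.2 ng/mL from both rises gives 5.3-11.3 (A), 13.1-18.7 (B) and 26.1-31.3 months (C). The two defects are separate.

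**The case against.** The strongest reply is that the text refers only to the time of relapse. It does not say the first relapse, and nowhere does it say that values are pooled across treatments. A man whose PSA fell after salvage treatment and rose again has relapsed again, and on that reading the rule gives the right answer. This stands: the text is ambiguous and does not mandate pooling. A reader might infer that men are being wrongly excluded. The document does not support that, because it neither fixes that reading nor says how many men have such a history. Exclusion is also not the general result even under pooling, as series A and most of B show.

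The unit is probably a misprint: the testosterone limit beside the PSA range is in ng/dL. A site that reads it as ng/mL suffers no harm from it. That also stands, but a figure that drives eligibility should not depend on sites guessing.

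A reader might also suspect bias in the trial result. PSADT is fixed before allocation by the same rule for both arms, and the primary Fisher's exact test is described without stratification. Misclassification therefore weakens balance on one minimisation factor but does not bias the comparison.

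Lastly, this is a journal article, and the full protocol may hold a detailed PSADT rule. That could settle the window, but the article states the method and prints the unit, and both need reconciling as they stand.

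**Conclusion.** The concern holds in a limited form. The unit conflict is certain: it is a factor of 100 against the scale used for all other PSA values. Its effect, if followed literally, is a possible shift into the slower stratum, shown here for a true PSADT of 3-5 months on one assumed series.

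The missing choice of relapse is a real ambiguity for a group that the eligibility criteria admit. Read as the current relapse, it does no harm. Read as the earliest, it inflated PSADT in every series shown: 17 of 18 results lay between about 5 and 25 months and one was 30.6, for a true 3-10 months. Seven of the 18 passed the 15-month limit. These sizes rest on assumed PSA histories and vary with the length of the first rise, the suppressed period and the height of the second rise. They are not estimates for this trial, and the share of men affected cannot be derived from the document. The primary comparison, its type I error and the 85% power are not affected.

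**What to change.** Amend the PSADT sentence in the Inclusion criteria in three ways:

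- Reconcile the unit of the relapse threshold with the ng/mL used for the other PSA values.
- State that PSADT uses only PSA values from the current rise after the last prostate-directed treatment (surgery, radiation, salvage radiation or ADT), with no values taken on ADT.
- State that this one value serves both eligibility and minimisation.

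There is no need to ask for dated past testosterone results. The criteria require only an entry level, and older results may not exist.

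The cost is a short wording change. The downside is fewer PSA values per man, and so a somewhat noisier PSADT where the current rise is short; in the assumed series the smallest count was 4.

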#### Exclusion criteria

No more than 3 years of ADT is allowed, with the most recent ADT treatment having occurred greater than 6 months prior to enrollment.
^18^F-DCFPyL-PET/MRI or ^18^F-DCFPyL-PET/CT scan within the past 6 months with results that demonstrate lesions not seen on baseline CT or bone scanCastration-resistant prostate cancer (CRPC).Spinal cord compression or impending spinal cord compression.Suspected pulmonary and/or liver metastases (greater > 10 mm in largest axis).Receipt of any other investigational agents or participation in a concurrent treatment protocol.Serum creatinine and total bilirubin > 3 times the upper limit of normalLiver Transaminases > 5-times the upper limit of normal.Inability to lie flat during or tolerate PET/CT, PET/MRI or SABR.Refusal to sign informed consent.

### Evaluation of randomization and blinding

This study will employ a randomized phase II design to determine the appropriateness of a subsequent phase III trial based on comparison of rate of progression at 6 months. An interactive web response system (IWRS) will be utilized to obtain the patient’s randomization assignment. Randomization will occur in a 2:1 fashion for SABR and observation arms, respectively. A minimization approach [35] will be applied to ensure balanced assignment to each treatment arm by: 1) Initial treatment with surgery vs. radiation therapy; 2) Prior hormonal therapy vs. no prior hormonal therapy; and 3) PSADT <6 mos vs. 6-14.9 mos. The on-study date for protocol entry will be the day that the study subject is randomized. Patients will be re-evaluated for radiographic response 6 months after randomization. Trial radiologists evaluating for treatment responses will be blinded to the treatment group and treatment specifics. The trial radiologists and the principal investigator will be unblinded only if a patient progresses at any time during the study.

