**Methods/design:**

Patients will be randomized 2:1 to SABR or observation with minimization to balance assignment by primary intervention, prior hormonal therapy, and PSA doubling time. Progression after 6 months will be compared using Fisher’s exact test. Hazard ratios and Kaplan-Meier estimates of progression free survival (PFS), ADT free survival (ADT-FS), time to locoregional progression (TTLP) and time to distant progression (TTDP) will be calculated based on an intention-to-treat. Local control will be assessed using Response Evaluation Criteria in Solid Tumors (RECIST) 1.1 criteria. Withdrawal from the study prior to 6 months will be counted as progression. Adverse events will be summarized by type and grade. Quality of life pre- and post- SABR will be measured by Brief Pain Inventory.

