Site-specific grade 4/5 toxicity will be monitored in the SABR arm. If it becomes evident that the proportion of grade 4/5 toxicity at specific sites convincingly exceeds 20%, the study will be halted for a safety consultation. Specifically, we will apply a Bayesian toxicity monitoring rule that suspends the enrollment for a posterior probability ≥ 75% of toxicity being larger than 20%. The monitoring rule uses Beta (0.5, 5.5) as prior distribution, meaning our prior guess of the proportion of toxicity is 8.3% with a 90% chance that this proportion is 0.04%-30.6%.

Follow-Up:Patients will be followed from Day 1 to Day 180.All AEs and serious adverse events (SAEs) are recorded on source documents. The investigator will follow up on all AEs and SAEs until the events have subsided, returned to baseline or, in case of permanent impairment, until the condition stabilizes.

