##### 2.4.2.2.Analysis of secondary objectives

For safety analysis, adverse events will be summarized by type and grade.Hazard rate estimates and 95% confidence intervals as well as Kaplan-Meier (KM) estimates will be calculated for PFS, ADT-FS, TTLP and TTDP. The median PFS, ADT-FS, TTLP and TTDP will be reported.Each metastatic lesion will be considered a target lesion and independently evaluated for response using RECIST 1.1 or bone scan evaluation criteria below. The lesion will be coded as locally controlled if it is considered stable radiographic disease or if there is evidence of a partial or complete response. Local control assessment will start at three months following randomization and continuous assessment will be pursued during the follow-up period. The proportion of locally controlled lesions will be estimated using generalized estimating equations.QoL will be assessed using the Brief Pain Inventory form. An overall score will be calculated pre-treatment and at the time of the 2^nd^ radiologic reassessment. The change in score will be evaluated by paired t-test.

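### The response radiologists may be unblinded once a patient progresses, so a Day 180 scan that feeds TTLP and TTDP may be read with the arm known

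*Protocol article*

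**What the plan says.** The relevant statements are all in the protocol article.

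- **Blinding.** Under Evaluation of randomization and blinding: "Trial radiologists evaluating for treatment responses will be blinded to the treatment group and treatment specifics". The same paragraph then sets the exception: "The trial radiologists and the principal investigator will be unblinded only if a patient progresses at any time during the study". No other reader is named for scans taken after progression.
- **Imaging.** The same section says: "Patients will be re-evaluated for radiographic response 6 months after randomization". The visit schedule under Interventions lists follow-up imaging at Day 180 only, and its follow-up paragraph says: "Patients will be followed from Day 1 to Day 180".
- **Progression.** Under Analysis of primary objective it is a composite. One route is "a ≥ 25% increase in PSA from nadir (and by ≥ 2 ng/mL), requiring confirmation ≥ 4 weeks later (PCWG2 criteria"). Symptomatic progression, start of ADT and death also count, alongside radiologic progression.
- **Endpoints that use the scan.** Under Analysis of secondary objectives: "The median PFS, ADT-FS, TTLP and TTDP will be reported". The abstract's Methods/design paragraph adds that hazard ratios and Kaplan-Meier estimates for PFS, ADT-FS, "time to locoregional progression (TTLP) and time to distant progression (TTDP) will be calculated based on an intention-to-treat". Lesion-level local control is also estimated.

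**The concern.** In a trial where patients and treating staff know the arm, blinded reading is the stated safeguard for the imaging endpoints. The exception ties its removal to the trial's main outcome event and expressly includes the readers. The outcome is expected to be twice as likely per patient on observation as on SABR, so the chance that a scan is read unblinded would differ by arm.

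A man who has progressed on PSA alone has not necessarily had a locoregional or distant event. His Day 180 scan may be what decides whether he has one. If the reader knows the arm, judgements on equivocal new or enlarging lesions may shift, and the TTLP and TTDP comparisons may shift with them. The protocol gives no reason why a reader needs the arm at progression.

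**Working it through.** **Inputs** (Sample size and accrual): 36 SABR and 18 observation patients; 6-month progression 40% and 80%; one-sided Fisher's exact test at 0.05; stated power 85%.

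**The plan's own figure.** Enumerating both binomials (n = 18, p = 0.80; n = 36, p = 0.40) and rejecting when the one-sided Fisher p is at most 0.05 gives a power of 85.06%. The stated 85% reproduces, so the rates and arm sizes can be used as they stand.

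**Can progression be declared before the scan?** PSA is scheduled at Days 1, 90 and 180, and a rise must be confirmed at least 4 weeks later.

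- Rise first seen at Day 90: confirmed from 90 + 28 = Day 118, which is 180 − 118 = 62 days before the scan.
- Rise first seen at Day 180: confirmed from 180 + 28 = Day 208, after the scan.
- Symptoms or start of ADT: possible at any time.

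So the sequence is possible. On scheduled draws, the PSA route needs a qualifying rise already at Day 90.

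**Upper bound.** Expected progressors = arm size × planned rate.

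- Observation: 18 × 0.80 = 14.4 men, 80% of the arm.
- SABR: 36 × 0.40 = 14.4 men, 40% of the arm.

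The per-patient ratio is 0.80 / 0.40 = 2, and the expected counts are equal. At these rates the chance that observation has more progressors than SABR is 0.447, and that SABR has more is 0.436.

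**Range below the bound.** Let f be the share of 6-month progressors declared before the scan. The documents do not give f. It is assumed here to be the same in both arms. Affected share = f × rate; affected men = f × 14.4.

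| f (assumed) | Observation | SABR |
|---|---|---|
| 25% | 20% (3.6 men) | 10% (3.6 men) |
| 50% | 40% (7.2 men) | 20% (7.2 men) |
| 75% | 60% (10.8 men) | 30% (10.8 men) |
| 100% (bound) | 80% (14.4 men) | 40% (14.4 men) |

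The ratio stays at 2 for any common f. Men who die or withdraw before Day 180 also count as progressed but would ordinarily have no Day 180 scan, so the bound would not be reached in practice.

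**The case against.** The strongest case against is that this is a loose sentence with little reach. Several parts of that case stand.

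- **Mandatory unblinding.** A reader might infer that the radiologists must be told the arm at every progression. The text says only if, which sets a limit. It permits unblinding at progression and does not clearly order it.
- **Many later scans.** Only one follow-up scan is scheduled, and it falls when follow-up ends. Progression first found on that scan leaves no later scheduled read to bias. The analysis section speaks of assessing local control from three months, but the visit schedule lists no Day 90 imaging.
- **Far more unblinded reads on observation.** This is true per patient (80% v 40%) but not in number of men (14.4 v 14.4).
- **Local control biased between arms.** It is stated as control after SABR, with no arm comparison described. Knowing that a lesion was irradiated could still colour a call of stable or progressive, but that affects a single-arm estimate.
- **The primary endpoint.** A later read cannot reclassify a man already counted as progressed. Only unblinding across the whole trial would reach other patients' reads. The sentence does not rule that out, but does not say it either.
- **Definitions and modality.** TTLP and TTDP are not defined in the article, so their dependence on the Day 180 scan is an inference, though a natural one. Day 180 imaging also differs by arm (bone scan with CT/MRI on observation, bone scan with PSMA-targeted PET on SABR), so a reader who sees the full set might guess the arm anyway.

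One part does not stand: that TTLP and TTDP are purely descriptive. The abstract plans hazard ratios for them, and a hazard ratio compares the arms. The difference in modality is a further weakness in the blinding, not a reason to disclose the arm.

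**Conclusion.** The point holds in a limited form. The protocol permits the response readers to be unblinded on an outcome that can precede the scan they still have to read. At the planned rates, at most 80% of observation and 40% of SABR patients could be affected. The true share is lower and cannot be computed from the documents.

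This rests on three assumptions: the planned rates hold, the men affected still have the Day 180 scan, and that scan contributes to TTLP and TTDP. The twofold ratio also assumes that the share declared early is the same in both arms. The direction and size of any resulting bias cannot be derived. The documents do not support concluding that the primary comparison is compromised; the exposure is to secondary imaging endpoints. It is worth correcting because the loss of blinding depends on outcome, serves no stated purpose and is easily avoided.

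**What to change.** Under Evaluation of randomization and blinding:

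1. Remove the trial radiologists from the unblinding sentence.
2. State that response readers stay blinded to arm until all of a patient's study scans are read, whether or not that patient has progressed.
3. Confine any unblinding at progression to the individual patient concerned and to staff who do not read scans.

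This is a change of one or two sentences. Sample size, power, visits and patient management stay the same. Readers need not be blinded to PSA or clinical status: the protocol does not promise that, and its response categories combine lesion and PSA criteria. The change stops the permitted disclosure of the arm; it does not remove what a reader could infer from the different Day 180 imaging in the two arms.
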